**Fig. 1 Fig1:**
[figure not shown]
Study flow diagram

### Study population

Consecutive patients with respiratory and/or constitutional symptoms suggestive of pulmonary TB who self-present to either of two local TB clinics will be offered recruitment into the study. The expected timeline to recruit the target number of patients is 1–2 years.

The eligibility criteria are:
age over 13 years (corresponding to increasing TB prevalence)suspected TBwritten, informed consent (parental consent and patient assent for those aged under 18 years)

### Bioaerosol collection

Bioaerosol specimens will be collected by two sampling methods. In addition, exhaled breath will be simultaneously sampled for aerodynamic particle counting and the CO_2_ concentration of sampled air will be measured. Ozone sterilization and empty RASC sampling will be carried out between every participant to provide negative controls.

### Direct sampling

A direct sampling protocol was developed by modifying the RASC [8]. Briefly, the RASC is a micro-environment designed for investigation of respiratory bioaerosol emissions from a single individual (see Fig. 2). This small personal clean space accommodates a seated participant during sampling. Modified from earlier descriptions, a metallic elliptical cone has been incorporated into which the participant can comfortably place their head at the larger open end. A unidirectional airflow is created by connection of a high-flow (250 l per minute) bespoke cyclone collector connected at the cone apex which extracts bioaerosol into a sterile phosphate-buffered solution. Air enters the collector via a tangential nozzle which generates a liquid cyclone with particle inertia leading to deposition of bioaerosol from the airstream onto the wet wall. The exit airflow from the cone will reaches a velocity of 12.5 m per second, enabling full collection of all expiratory respiratory particles including those generated during forceful coughing. Participants, who will be seated in the HEPA-filtered chamber, will be required to perform a specific breathing protocol with regular instruction by a study nurse. The protocol will consist of a series of 15 vigorous coughs every 20 s (5 mins), a period of tidal breathing (5 mins) and a further series of 15 bronchiole burst manoeuvres (BBM) every 20 s (5 mins). A BBM consists of two deep breaths with full exhalation on each breath. Figure 3 illustrates computational fluid dynamic modelling demonstrating complete sampling of high-velocity respiratory manoeuvres without backflow from the cone. Collection of entrained bioaerosol from the respiratory activities to a small volume of liquid enables non-culture-based analytical methods as described below [7].

**Fig. 2 Fig2:**
[figure not shown]
Modified RASC with author wearing a Tyvek™ non-woven fabric suit

**Fig. 3 Fig3:**
[figure not shown]
Computational fluid dynamic modelling of the flow velocity streams at maximum cough strength with a collection air-flow rate of 300 l per minute

### Indirect sampling

Sampling of patient-derived respiratory bioaerosol during natural respiratory activity will also be performed in the same chamber without the use of the elliptical cone. This method is similar to a previous study [4] but has since been adapted to improve sensitivity [11]. In order to replicate a real-life transmission environment the entire volume of the RASC concentrates exhaled air leading to a variable dwell period with particle ageing prior to collection. This sampling takes place over a 60-min period following the direct sampling protocol. The high-flow cyclone collector continuously samples chamber air extracting bioaerosol into a sterile phosphate-buffered saline solution.

### Microscopy-based detection of *Mtb*

The pellet from the centrifuged bioaerosol sample is stained using the solvatochromic trehalose probe, DMN-trehalose, which is incorporated as trehalose monomycolate into the cell walls of metabolically active *Corynebacteriaceae* (including *Mycobacterium*) by the antigen 85 protein complex [12]. After overnight incubation in media containing DMN-trehalose, the samples are washed and added to a novel nanowell device described in ref. [9]. The devices are sealed with adhesive film and centrifuged prior to visualization by fluorescence microscopy. Detection, enumeration and differentiation from debris of fluorescent bacilli is based on dye incorporation patterns and differential bacterial cellular morphology (cell length and width) [9].

### Droplet digital polymerase chain reaction (ddPCR) detection of *Mtb*

DNA from *Mtb* bacilli is extracted using an in-house lysis buffer with subsequent pelleting of DNA (by centrifugation at 9000 x g for 10 min), discarding of supernatant, and resuspension in 20 μl of Tris-EDTA buffer (10 mM Tris, 1 mM EDTA, pH 8.0). Given that ddPCR is relatively robust against inhibitors, no further DNA purification is required. The primer/probe combinations and reaction conditions for *Mtb* specific ddPCR have been described previously [4]. Serial dilutions of known concentrations of purified *Mtb* H37Rv genomic DNA are included as positive internal controls for ddPCR, and nuclease-free water is included as a negative control. Data generated from the ddPCR reaction are analyzed via the Umbrella pipeline [13] using only wells for which a minimum of 10,000 droplets have been detected.

### Mass spectrometry detection of *Mtb*

The supernatant from the centrifuged bioaerosol sample is lyophilized followed by lipid extraction by the Folch method. Samples are introduced into an LTQ Orbitrap Mass Spectrometer (Thermo Fisher Scientific) via electrospray ionization by direct infusion. Positive and negative ion calibration solutions are used to optimize ion source conditions and mass calibration. For data acquisition, resolving power of 60,000 at 200 m/z is used for both positive and negative ions in the mass range 200–2000 m/z.

### Statistical analysis

Historical clinic data suggest individuals suspected of TB divide into groups A, B, and C in the ratio 3:5:10. Based on this ratio, a sample size of 250 TB clinic attendees will give a 90% power to detect a 20% bioaerosol yield in Group B. Assuming 100% bioaerosol yield in Group A, this gives an absolute difference of 12.5% between sputum and bioaerosol yields in notified TB cases (two-sided *p* < 0.05).

Demographic (age, sex, BMI, HIV status) and microbiology data will be entered into a secure RedCap Database. To maintain confidentiality, participant identifying information will be removed. All analyses will be based on the groups to which patients are originally assigned. Analyses of the primary and secondary aims will be by comparison of paired proportions using McNemar’s test or comparison of independent proportions using a chi-square test. Mixed effect models can be used to adjust comparisons for any potential confounding variables.

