#### Primary objective

To compare the prevalence proportions of *Mtb*-containing bioaerosol in sputum-positive and sputum-negative pulmonary TB cases (Groups A & B).

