## Methods

### Study design

This study will utilize a pragmatic, parallel group design (Fig. 1). All participants who meet the eligibility criteria will be invited to have bioaerosol sampling performed at the Aerobiology Research Centre (ARC) prior to TB investigations or treatment. An induced sputum sample will be collected, cultured and stored for future downstream studies before bioaerosol sampling. Classification into three groups will be based on the outcome of routine clinical practice at the TB clinic implementing the National TB Control Program (NTBCP) [10]. Group A will comprise patients with TB notification and sputum-based laboratory confirmation (GeneXpert positive sputum or sputum culture if performed); Group B will consist of patients with TB notification without sputum-based laboratory confirmation (physician diagnosed cases with GeneXpert negative sputum and negative sputum culture if performed); and Group C will contain individuals who are not notified. Repeat bioaerosol sampling will be conducted after 14 days on participants in all groups with initial bioaerosol samples containing viable *Mtb*. Group C individuals will be re-evaluated clinically, with induced sputa and repeated bioaerosol sampling at monthly intervals until two consecutive samples are negative or treatment is commenced.

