To our knowledge, bioaerosol sampling in sputum-negative pulmonary TB cases has not been performed previously, despite evidence of transmission from this group [15–18]. We are therefore extending attempts to detect bioaerosol to patients with notified TB without sputum microbiological confirmation (Group B). Expectorated sputum, the primary specimen for pulmonary TB diagnosis, has significant limitations [19]. Globally, only 56% of pulmonary TB cases are bacteriologically confirmed by sputum testing [20]. The remainder, who are diagnosed by clinical symptoms or chest radiography, do not accumulate *Mtb* bacilli in sputum, or do not produce sputum, or do not expectorate adequately. Poor quality sputum samples are a particular problem in children and in HIV-infected individuals, leading to suboptimal diagnostic sensitivity. The finding of culture or Xpert MTB/RIF positivity in bronchoalveolar lavage from sputum-negative or sputum-scarce patients [21–23] suggests that *Mtb* is frequently present in the peripheral airways. The bronchiole fluid film burst method of bioaerosol generation [7] rapidly and non-invasively samples this biofluid with comparable biosafety to induced sputum. We aim to provide preliminary data on the clinically relevant role of bioaerosol sampling as a novel diagnostic specimen.

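### Group B is labelled sputum-negative but defined by routine results only, and the study's own baseline induced-sputum culture is not used to check the label

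*Protocol article*

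**What the plan says.** The Primary objective is to compare the prevalence of *Mtb*-containing bioaerosol "in sputum-positive and sputum-negative pulmonary TB cases (Groups A & B").

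The Study design section builds the groups differently: "Classification into three groups will be based on the outcome of routine clinical practice at the TB clinic". Confirmation for Group A is "GeneXpert positive sputum or sputum culture if performed". Group B consists of "physician diagnosed cases with GeneXpert negative sputum and negative sputum culture if performed". Culture therefore counts in both definitions, but only for patients whose clinic ordered one.

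The same section describes a further specimen: "An induced sputum sample will be collected, cultured and stored for future downstream studies before bioaerosol sampling". The article nowhere uses the result of that baseline culture to classify participants or in an analysis.

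The Statistical analysis section adds: "All analyses will be based on the groups to which patients are originally assigned". It does not say when assignment becomes final.

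**The concern.** The label and the definition of Group B do not match. A notified, GeneXpert-negative patient who was never cultured by the clinic is counted as sputum-negative, even if the study's own induced sputum, taken before bioaerosol sampling, grows *Mtb*. The Discussion makes this plausible. It attributes missing sputum confirmation partly to patients who produce no sputum or expectorate poorly, and it describes poor-quality samples as "leading to suboptimal diagnostic sensitivity". Induction is aimed at exactly those patients.

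The label also carries the main message. The Discussion presents bioaerosol sampling of sputum-negative pulmonary TB as new. If part of the Group B yield comes from patients with culturable *Mtb* in their sputum, that part is not evidence about sputum-negative disease.

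**Working it through.** **Inputs from the article**
- Statistical analysis: 250 attendees; "individuals suspected of TB divide into groups A, B, and C in the ratio 3:5:10"; 20% bioaerosol yield in Group B; 100% assumed in Group A; a 12.5-point difference between bioaerosol and sputum yields in notified cases.
- Background: published yields of 28% to 77% in sputum-positive patients.

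**Input not in the article**
- m, the share of Group B positive on the study's induced-sputum culture. Assumed here at 5%, 10% and 20%.

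**Step 1: the plan's own figure**
- Group A: 250 × 3/18 = 41.7. Group B: 250 × 5/18 = 69.4. Notified: 111.1.
- Sputum yield: 41.7/111.1 = 37.5%.
- Bioaerosol yield: (41.7 + 0.20 × 69.4)/111.1 = 50.0%.
- Difference: 12.5 points, as stated. It treats every Group B patient as sputum-negative.

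The stated 90% power is a separate matter; nothing below depends on it.

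**Step 2: effect on the Group B yield**

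Let yA be the bioaerosol yield of the culture-positive patients in Group B and y the yield of the true negatives.
- Observed Group B yield = m·yA + (1 − m)·y.
- Overstatement = m·(yA − y), which is upward whenever yA exceeds y.
- With 20% observed, y = (0.20 − m·yA)/(1 − m).

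| m (assumed) | yA = 100% | yA = 77% | yA = 28% |
|---|---|---|---|
| 5% | 0.150/0.95 = 15.8% | 0.1615/0.95 = 17.0% | 0.186/0.95 = 19.6% |
| 10% | 0.100/0.90 = 11.1% | 0.123/0.90 = 13.7% | 0.172/0.90 = 19.1% |
| 20% | 0/0.80 = 0% | 0.046/0.80 = 5.75% | 0.144/0.80 = 18.0% |

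**Step 3: effect on the gain over sputum**

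Hold the bioaerosol results fixed at 50.0% and count the culture-positive Group B patients as sputum-positive. Each adds one to the sputum count, whatever that patient's bioaerosol result.
- Gain = 50.0 − (41.7 + 69.4·m)/111.1 × 100 = 12.5 − 62.5·m points.
- m = 5%: 9.4 points. m = 10%: 6.25, about 6.3 points. m = 20%: 0 points.

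If the comparator is routine clinic sputum alone, the sputum count does not change and the gain stays at 12.5 points.

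**The case against.** A reader might infer that the sentence on original assignment freezes a patient in Group B even when a clinic culture later turns positive, so that it contradicts the group definitions. The article does not establish this. It gives no time point, and routine culture is part of both definitions, so original assignment may well mean the completed routine classification. The sentence also does useful work. Bioaerosol-positive Group C participants are re-evaluated with further induced sputa, and without such a rule they could change group because of the very test under study.

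A reader might also infer that the plan does leave culture-positive patients in Group B and does inflate its yield. That too goes beyond the article, which gives no culture-positive rate for Group B. The effect on Group B yield may be small: the Background warns that paucibacillary patients may fall below the detection threshold, and at m = 5% and yA = 28% the shift is 0.4 points.

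Programme-based grouping is a declared pragmatic choice. The Discussion also describes Group B as notified TB without microbiological confirmation in sputum. For that population the yield is not biased, and a patient missed by clinic sputum but found in bioaerosol is a real gain.

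Finally, this is a condensed article, and sensitivity analyses are often left to fuller documents. All of this limits the point but does not remove it. The definitions, the label in the primary objective and the stated purpose of the culture are all given in the article, and they do not fit together.

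**Conclusion.** The point holds as a mismatch between label and definition that can bias a claim about sputum-negative TB. It is not a demonstrated bias, and the classification rule in Study design is its main source, not the sentence on original assignment.

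The size depends on two unknowns. Over the assumed 5% to 20% culture-positive share, a 20% observed Group B yield could correspond to anything from 19.6% down to 0% in true negatives; the lower end requires every culture-positive patient to be bioaerosol-positive. The loss of 3.1 to 12.5 points from the planned gain, when those patients count as sputum-positive, depends on their share alone. The upward direction for the Group B yield requires sputum-positive patients to yield more than sputum-negative ones, as the plan's own 100% and 20% assume. Conclusions limited to notified cases without routine sputum confirmation are not affected.

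**What to change.** Keep the programme-based groups and make two changes.

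1. In Statistical analysis, define the rule on original assignment. Suggested wording: *Group membership is the final routine classification from baseline sputum, including any clinic culture; findings prompted by a positive bioaerosol result do not change it.*
2. Add the primary comparison with Group B restricted to participants negative on the study's baseline induced-sputum culture. Base any sputum-negative claim on that version. Elsewhere, describe Group B as notified without routine sputum confirmation.

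The cost is a wording change and one further analysis, using cultures already planned. Group B becomes slightly smaller: at the assumed shares, 69.4 falls to 66.0, 62.5 or 55.6, that is 69.4 × (1 − m). Its yield may also be lower.

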**Methods:**

Our parallel-group design will identify viable *Mtb* in bioaerosols produced by individuals attending a TB clinic in South Africa. Sampling will be performed on eligible individuals presenting with symptoms indicative of TB and repeated at 14 days if initially positive. Participants will be prospectively classified into three distinct groups based on National TB Control Program (NTBCP) criteria: Group A, TB notification with sputum-based laboratory confirmation; Group B, TB notification with empiric diagnosis; and Group C, individuals not notified. Group C individuals with detectable *Mtb* bioaerosol will be monitored until resolution of clinical and laboratory status. Collection of bioaerosol specimens will be via two consecutive sampling modalities: (1) direct sampling following a specific respiratory manoeuvre; and (2) indirect sampling during passive respiratory activity. Bioaerosol specimens will be analyzed for viable *Mtb* using DMN-trehalose staining and live-cell fluorescence microscopy. *Mtb* genomes and mycobacterial and host lipids will be detected using droplet digital PCR and mass spectrometry analyses, respectively. The primary objective is to determine the prevalence of *Mtb* bioaerosols in all TB clinic attendees and in each of the groups. Secondary objectives are to investigate differences in prevalence of *Mtb* bioaerosol by HIV status and current isoniazid preventive therapy (IPT) use; we will also determine the impact of anti-TB chemotherapy on *Mtb*-containing bioaerosol production.

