#### Secondary objectives

2.To quantify the numbers of viable *Mtb* organisms in bioaerosols per litre of air sampled and per nanolitre of bioaerosol particulate volume collected in both sputum-positive and sputum-negative pulmonary TB cases (Groups A & B).

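### The secondary objective is a concentration of viable *Mtb*, but the plan assigns it to tests of proportions, which cannot estimate or compare a concentration

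*Protocol article*

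**What the plan says.** Four places in the protocol article bear on this.

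- **Secondary objectives.** The single item is to quantify viable *Mtb* "organisms in bioaerosols per litre of air sampled and per nanolitre of bioaerosol particulate volume collected", for Groups A and B.
- **Microscopy-based detection of *Mtb*.** "Detection, enumeration and differentiation from debris of fluorescent bacilli is based on dye incorporation patterns" and on cell morphology. Bacilli are therefore counted, and count data will exist.
- **Statistical analysis.** "Analyses of the primary and secondary aims will be by comparison of paired proportions". The tests named are McNemar's for paired data and chi-square for independent groups. The only other model named is optional: "Mixed effect models can be used to adjust comparisons for any potential confounding variables".
- **Abstract, Methods.** "Secondary objectives are to investigate differences in prevalence of" *Mtb* bioaerosol by HIV status and IPT use, together with the effect of anti-TB chemotherapy. In the body, all three comparisons stand under Exploratory objectives.

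**The concern.** The plan does not leave the method for its secondary aim open. It names one, and that one does not fit the endpoint. A McNemar or chi-square test takes a yes/no outcome. To use either on this objective, each participant's count must be reduced to detected or not detected, and that is the primary objective again (prevalence in Groups A and B).

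What would be lost is the estimate itself: organisms per litre and per nanolitre, by group, with a measure of uncertainty. The Discussion treats the number of viable bacilli from indirect sampling as a possible reflection of host infectivity, so load is a question that the study wants answered and not a by-product. An analysis plan that followed the sentence literally would carry the mismatch forward.

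**Working it through.** **1. Objective and method side by side**

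| | Objectives section | Statistical analysis section |
|---|---|---|
| Primary | Prevalence proportions, A v B | McNemar or chi-square: fits a proportion |
| Secondary | Organisms per litre and per nanolitre, A and B | McNemar or chi-square: does not fit a concentration |

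The mixed-model sentence does not close the gap. It is optional, it concerns confounding, and it names no count or rate outcome.

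**2. The plan's own figures.** Inputs from Statistical analysis: 250 attendees, ratio A:B:C of 3:5:10, yield 100% in A and 20% in B.

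- Group A: 250 × 3/18 = 41.7. Group B: 250 × 5/18 = 69.4. Notified cases: 111.1.
- Extra positives from B: 0.20 × 69.4 = 13.9. Then 13.9/111.1 = 12.5%, so the stated difference reproduces.
- The stated 90% power does not reproduce. The McNemar normal approximation with 111 pairs, Φ[(0.125√111 − 1.96√0.125)/√(0.125 − 0.125²)], gives 97.0%. The present point does not depend on it.

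**3. What positivity can say about load under those yields**

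- Expected positives: 41.7 in A + 13.9 in B = 55.6. Group A holds 41.7/55.6 = 75% of them.
- In Group A the variance of the positive/negative indicator is p(1 − p) = 1 × 0 = 0. Every participant has the same value, whatever the count.

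**4. Illustration, not a property of this trial.** The documents give no count distribution. The following assumes log-normal counts among positives with log SD 1, 42 v 69 participants and 4,000 runs. It shows the proportion of runs significant at two-sided 0.05.

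| Yield A / B | Median count in positives, A v B | Chi-square on positivity | Rank test, positives only | Rank test, all counts |
|---|---|---|---|---|
| 100% / 20% | 10 v 5 | about 100% | 54% | about 100% |
| 100% / 20% | 10 v 10 | about 100% | 5% | about 100% |
| 90% / 90% | 10 v 5 | 5% | 89% | 77% |
| 80% / 80% | 10 v 5 | 5% | 85% | 56% |
| 50% / 50% | 10 v 5 | 5% | 65% | 15% |

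The chi-square result follows yield and ignores load. At the plan's yields it is significant whether or not load differs. At equal yields it stays at its nominal 5% even with a twofold difference in load. The first two rows also show that a rank test on all counts, zeros included, mainly picks up prevalence when yields are far apart. The same holds for a mean over all participants: with equal mean load m among positives, the A:B ratio would be (1.0 × m)/(0.2 × m) = 5.

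**5. Litres as denominator.** Direct sampling describes a "high-flow (250 l per minute) bespoke cyclone collector". The caption of Fig. 3 gives modelling "with a collection air-flow rate of 300 l per minute". Over the 15 minutes of direct sampling this is 3,750 l or 4,500 l, a factor of 1.2. A common error in flow multiplies both groups' litres equally and cancels in an A:B rate ratio. The per-nanolitre measure does not use litres at all.

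**The case against.** - **The sentence may have been written for the abstract's list.** Chi-square fits prevalence by HIV status and IPT use, and McNemar can fit positivity before and after treatment. This is plausible and may explain the mismatch. It does not remove it: the body's secondary objective then has no matching method, and the two lists still disagree.
- **The objective says quantify, not compare.** This stands. No between-group test of load is required, and estimates with intervals would satisfy the objective. A test of proportions supplies neither.
- **A count method may be left to an analysis plan that is not shown.** That would answer a complaint that the method is missing. Here a method is stated for the secondary aim, and it is of the wrong kind.
- **Stronger readings are not supported.** A reader might infer that the plan throws away most of the information, or a specific amount of power. That depends wholly on assumed counts. For example, negative binomial means of 10 v 3 with k = 0.5 give 40% power for chi-square and 88% for a rank test on counts. But they imply Group B positivity of 1 − (0.5/3.5)^0.5 = 62%, against the plan's 20%. At the plan's yields the contrast disappears.
- **The exploratory counts.** A reader might also infer that the exploratory objectives on counts would go unanswered. The sentence covers only primary and secondary aims, so it assigns those no method, right or wrong.
- **The flow figures.** It is tempting to say that every per-litre value is uncertain by 20%. One figure is the collector's flow and the other a modelling condition. The error would arise only if samples were taken at one flow and divided by the other, which nothing in the article says.

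**Conclusion.** The point holds in a limited form. The stated method does not fit the one secondary objective in the body of the article, and following it would duplicate the primary analysis and yield no concentration. This rests on the text alone. The 75% share of expected positives with no variation in positivity rests on the plan's assumed yields and ratio.

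The size of any loss in power cannot be stated for this trial. The primary analysis is unaffected, and the counts are collected anyway, so nothing is irrecoverable. It should be corrected before analysis. The 250 and 300 l/min figures need at most a clarifying sentence.

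**What to change.** 1. Limit McNemar and chi-square in the analysis sentence to prevalence outcomes.
2. For the secondary objective, report organisms per litre and per nanolitre in Groups A and B, each with a 95% CI. Say whether this is over all participants or among positives, since the two answer different questions when yields differ.
3. If A and B are compared, give a rate ratio with 95% CI from a count model. A negative binomial model is suitable, in hurdle form if zeros are in excess, with log sampled volume or log particulate volume as offset. Within one sampling method at fixed flow and duration, log litres is constant and only shifts the intercept. The offset matters for particulate volume, and for litres wherever recorded volumes differ.
4. Reconcile the secondary objectives in the abstract with the secondary and exploratory lists in the body.
5. State which flow rate applied during sampling, and that the Fig. 3 value is a modelling condition if that is so.

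The cost is a change of wording and modest extra analysis. No new data, visits or participants are needed.
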